### Methods for additional analyses

Exploratory subgroup analyses will assess treatment effects by ulcer etiology (VLU vs. VLU + PAD), baseline ulcer size, and center. Interaction terms will be included in the model; results will be interpreted cautiously as hypothesis-generating.

### Methods in analysis to handle protocol non-adherence and missing data

Analyses will follow the intention-to-treat principle. Missing outcome data will primarily be analyzed as observed and may be addressed using multiple imputation under the assumption of data being missing at random. Participants who deviate from protocol will remain in ITT unless withdrawn for safety.

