### Visit schedule

Participants attend visits at screening (week −2), baseline/randomization (week 0), and follow-ups at weeks 2, 4, 6, 8, 10, 12, 16, 20, and 24. Each visit includes ulcer assessment, wound photography, compression therapy documentation, changes in concomitant medications/therapies documentation, economic parameters documentation, and adverse event monitoring. Health-related quality of life and pain (Visual Analog Scale (VAS)) are assessed at baseline (week 0) and after 3 months (week 12). The 24-week visit assesses longer-term healing outcomes and ulcer recurrence.

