### Outcomes

#### Primary outcome

The primary outcome is PWAR at week 12 relative to baseline, measured via standardized planimetry with central blinded review.

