### Statistical methods

#### Statistical methods for primary and secondary outcomes

The primary endpoint (PWAR at week 12) will be analyzed using analysis of covariance (ANCOVA) adjusting for baseline ulcer area, ulcer type, and site. Binary outcomes (e.g., complete closure) will be assessed with logistic regression; time-to-event data (e.g., time to 100% closure) with Cox proportional hazards models; and repeated measures with linear mixed-effects models. The significance level is set at *α* = 0.05 (two-sided). Confidence intervals will be reported at 95%. All statistical analyses will be performed using Stata (version 16.1) and R (version 4.3.2).

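### The primary analysis drops participants without a week-12 area, leaves the earlier areas unused and makes imputation optional, so dropout that differs by arm can shift the estimate

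*Protocol article*

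**What the plan says.** All references are to the protocol article.

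- **Endpoint** (Primary outcome): "The primary outcome is PWAR at week 12 relative to baseline".
- **Primary model** (Statistical methods for primary and secondary outcomes): the endpoint is "analyzed using analysis of covariance (ANCOVA) adjusting for baseline ulcer area, ulcer type, and site". No post-baseline area enters this model. The same paragraph lists "repeated measures with linear mixed-effects models", but not for the primary endpoint.
- **Analysis principle and missing data** (Methods in analysis to handle protocol non-adherence and missing data): "Analyses will follow the intention-to-treat principle". Then: "Missing outcome data will primarily be analyzed as observed and may be addressed using multiple imputation", the imputation assuming missing at random. Then: "Participants who deviate from protocol will remain in ITT unless withdrawn for safety". The abstract repeats the missing-data rule.
- **Data available** (Visit schedule): "follow-ups at weeks 2, 4, 6, 8, 10, 12, 16, 20, and 24", with ulcer assessment and photography at each visit. Under Secondary outcomes, PWAR is a named outcome at weeks 4, 8, 12, 16, 20 and 24.
- **Follow-up after stopping treatment** (Plans to promote participant retention and complete follow-up): outcomes are still collected if the participant agrees to be observed.

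**The concern.** Taken together, these statements fix a complete-case analysis. An ANCOVA of week-12 PWAR, analysed as observed, has no place for a randomised participant whose week-12 area is missing. That sits uneasily with the intention-to-treat label.

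The areas from weeks 2 to 10 show how such a participant was healing before leaving. They could correct for dropout that follows healing, and they are collected anyway. The word *may* leaves open whether imputation is run at all, and the article gives no rule for when.

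Arm-dependent dropout is plausible here. Participants and clinicians know the allocation, the COMS arm attends two to three sessions a week for 8 weeks, and the device is commercially available to a control participant who wants it. At stake are the size of the week-12 difference and whether its missing-data handling was settled before the results were known.

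**Working it through.** **The plan's own figure.** Sample size gives a difference of 20 points (65% against 45%), SD 33, two-sided alpha 0.05, 90% power, 5% attrition and 61 per arm. Normal approximation: n = 2 × (1.960 + 1.282)² × (33/20)² = 57.2, so 58 per arm. Attrition: 58 × 1.05 = 60.9 (61), or 58/0.95 = 61.05 (62). The t-test version gives 58.19, and 58.19/0.95 = 61.25. The stated 61 is reproduced within rounding. Power (normal approximation) is 91.7% with 61 per arm and 90.4% with 58. At 5% attrition about 3 per arm are lost (0.05 × 61), so power is not the problem.

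**Bias by algebra.** In an arm with missing fraction d, full mean = (1 − d) × observed mean + d × missing mean. Hence observed mean − full mean = d × gap, where gap = observed mean − missing mean. For the treatment difference:

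bias = d(COMS) × gap(COMS) − d(SOC) × gap(SOC)

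The documents give no gap, so I assume 20 to 45 points, equal in both arms:

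- 5% / 5%: 0
- 5% COMS / 10% SOC: −0.05 × 20 = −1.0, to −0.05 × 45 = −2.3
- 5% COMS / 15% SOC: −0.10 × 20 = −2.0, to −0.10 × 45 = −4.5

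Swapping the arms reverses the sign. Extra loss of poor healers from SOC works against COMS; extra loss from COMS works in its favour.

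**Simulation.** Assumptions, none from the documents: normal PWAR at weeks 2 to 12, correlation 0.8 or 0.9 per two weeks, dropout after week 8, log-odds of dropout changing by 1 per SD, 200,000 per arm. The 20-point effect and SD 33 are the plan's. Monte Carlo error of a difference is 33 × √(2/200,000) = 0.10. Ranges span the two correlations. Dropout in the table depends on week-8 PWAR (missing at random, MAR).

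| Dropout COMS / SOC | Who leaves | As observed | Using weeks 2–8 |
|---|---|---|---|
| 5% / 5% | poor healers, both arms | 19.8–20.0 | 19.8–20.0 |
| 5% / 5% | unrelated on COMS, poor healers on SOC | 18.7–19.0 | 19.9–20.0 |
| 5% / 5% | good healers on COMS, poor healers on SOC | 17.6–18.1 | 20.1 |
| 5% / 10% | poor healers, both arms | 18.8–19.1 | 20.0–20.1 |
| 5% / 15% | poor healers, both arms | 17.5–18.4 | 19.8–20.2 |
| 5% / 20% | poor healers, both arms | 16.5–17.4 | 19.9–20.0 |

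The second row checks the algebra: shifts of 1.05 and 1.34 divided by 0.05 imply gaps of about 21 and 27 points, inside the assumed range. If rate and mechanism both differ (5% / 15%, with COMS dropout unrelated to healing or among good healers), the as-observed result is 15.2 to 17.1.

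**Not at random.** If dropout depends on the unseen week-12 value (MNAR), the last three rows become 15.8–18.6 as observed and 17.5–19.5 using weeks 2–8. At 5% / 5% with opposite mechanisms they are 16.9–17.0 and 18.1–19.0. Earlier visits reduce this bias but do not remove it.

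**Scale.** With 58 analysed per arm the standard error is 33 × √(2/58) = 6.1 points. A shift of 2.5 is 0.41 of that; 3.5 is 0.57.

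**The case against.** The strongest reply has five parts.

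1. *Bias is conditional.* A reader might infer that the planned analysis will be biased. The documents contain no evidence of dropout that differs by arm, and dropout that follows healing equally in both arms leaves the difference intact. This stands.
2. *The larger scenarios exceed the plan.* Dropout of 10 to 20% on SOC goes beyond the planned 5%, at which the MAR shift is under half a standard error. If disappointed SOC participants are the ones who leave, the error is conservative. This stands for size, but the direction is not guaranteed.
3. *Intention-to-treat is not flatly contradicted.* A reader might say that it is. But participants who deviate are kept, and outcomes are sought after treatment stops, so only those not observed at week 12 are lost. The label still does not describe an analysis of everyone randomised, and the exception for safety withdrawals is the plainer conflict.
4. *Two primary answers are not left open.* A reader might infer this from *may*. The text does name as-observed as primary; what is open is whether imputation follows. Masked treatment codes until database lock also limit a choice driven by arm, though not afterwards.
5. *Detail belongs in the statistical analysis plan, and the simulation is crude.* An imputation model or covariance structure is not missing from a condensed article, and ANCOVA at one time point is an accepted primary analysis. The simulation omits the ANCOVA covariates and lets PWAR exceed 100% (about 14% of COMS values at mean 65, SD 33). Its figures are therefore indicative only. The point concerns a method that the article states, not one that it leaves out.

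**Conclusion.** The point holds as a cheap improvement to a stated method, not as a fault that invalidates the trial. The primary estimate rests on participants observed at week 12, ignores areas already collected, and leaves the alternative optional.

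The possible shift on a 20-point effect, under MAR, is about 0 to 2.5 points at 5% attrition in each arm. It is about 1 to 3.5 points at 10 to 20% SOC dropout against 5% on COMS, when poor healers leave both arms. It is larger if mechanisms also differ or dropout is MNAR, and essentially nil if rate and mechanism are equal. The dropout split, mechanism and correlations are assumptions. The two-weekly series is ulcer assessment up to week 12; treating it as two-weekly PWAR is a small inference, since PWAR is a named outcome only every four weeks.

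**What to change.** Before unmasking, prespecify one primary method that uses the post-baseline areas up to week 12:

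- a repeated-measures mixed model of PWAR with treatment-by-visit terms and the ANCOVA covariates, taking the week-12 contrast as the primary estimate; or
- the planned ANCOVA after multiple imputation by arm that includes the earlier areas. This also keeps participants with no post-baseline visit, whom the mixed model would omit.

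Then make the as-observed ANCOVA and a delta-adjusted imputation, with less favourable values for dropouts, fixed sensitivity analyses. Replace *may* with *will*. Reconcile the intention-to-treat statement with the exception for participants withdrawn for safety, so that the analysis set is unambiguous.

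The cost is protocol and analysis-plan wording and somewhat more modelling; no new data are needed. A mixed model needs a stated covariance fallback in case it does not converge. Either method relies on MAR, which is why the delta-adjusted analysis is part of the fix.

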### Criteria for discontinuing or modifying interventions

Treatment discontinuation or modification will occur:Under emergency circumstances, based on his/her clinical judgment, the principal investigator at site may proceed to deviations from the CIP or study discontinuation to protect the rights, safety and well-being of the subjects, without prior approval by the Sponsor and the CEC. AEs related to the IMD and all SAEs must be reported and participants followed up until resolution of the event.If the scientific integrity of the investigation is compromised (noncompliance with the clinical trial protocol or GCP requirements from the part of the subject, the investigator, or the trial staff).If the participant decides to withdraw from the study.

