#### Safety outcomes

All serious adverse events (SAEs) will be reported. Only adverse events (AEs) related to the investigational medical device (IMD) and not related to the natural course of VLUs evolution will be reported. Severity and connection to the IMD will be categorized according to ISO 14155 definitions.

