## Assignment of interventions: blinding

### Who will be blinded?

Due to the visible nature of COMS treatment, participant and clinician blinding is not feasible.

However, blinding will be maintained for outcome assessors, data analysts, and the steering committee. Wound images will be coded using participant’s unique identification numbers, and blinded assessors will review them centrally without knowledge of treatment arm or site. Statistical analyses will be conducted using masked treatment codes until database lock.

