### Plans to promote participant retention and complete follow-up

Retention strategies include reminder calls for visits, flexible scheduling, and travel reimbursement (as permitted by local ethics). Participants who withdrew early will be invited for final data collection, and missing data will be minimized through prompt monitoring queries. Outcome data will be collected for all participants who discontinue intervention but consent to continued observation.

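### The intention-to-treat rule excludes participants withdrawn for safety, a post-randomisation exclusion that can fall unequally between the arms and could favour COMS

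*Protocol article*

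**What the plan says.** The section *Methods in analysis to handle protocol non-adherence and missing data* opens with the principle: "Analyses will follow the intention-to-treat principle". It then gives the missing-data rule: "Missing outcome data will primarily be analyzed as observed and may be addressed using multiple imputation under the assumption of data being missing at random". It closes with the exception: "Participants who deviate from protocol will remain in ITT unless withdrawn for safety".

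Four other places bear on how that exception would work:

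- *Plans to promote participant retention and complete follow-up*: "Outcome data will be collected for all participants who discontinue intervention but consent to continued observation".
- *Who will be blinded?*: "participant and clinician blinding is not feasible". Only outcome assessors, analysts and the steering committee are masked.
- *Criteria for discontinuing or modifying interventions*: in an emergency and to protect participants, "based on his/her clinical judgment, the principal investigator at site may proceed to deviations from the CIP or study discontinuation".
- *Safety outcomes*: "All serious adverse events (SAEs) will be reported", which covers both arms. For other events, "Only adverse events (AEs) related to the investigational medical device (IMD) and not related to the natural course of VLUs evolution will be reported". The control arm has no device, so in practice these arise only under COMS.

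**The concern.** Intention-to-treat protects the comparison because nothing that happens after randomisation decides who is analysed. The exception breaks that protection: it removes people because of an event that the treatment can cause, and unblinded staff and participants take part in the decision. Central blinded reading of wound images does not help, because the exclusion acts on who is counted and not on how the wound is measured.

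The exception also conflicts with the retention section. Someone who stops COMS for a safety reason and agrees to stay under observation may have a week-12 measurement, yet would be left out. Neither the as-observed analysis nor imputation restores a person who has been defined out of the set.

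At stake is the primary superiority test. If the people removed are mostly COMS participants whose ulcers did badly, the difference is shifted towards COMS and the type I error rises.

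**Working it through.** **Inputs from *Sample size*.** 61 per arm; mean percentage wound area reduction (PWAR) 65% with COMS and 45% with standard care; SD 33; two-sided alpha 0.05; 90% power; 5% attrition.

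**The plan's own figure.** n per arm = 2 × (33 × (1.96 + 1.2816) / 20)² = 57.2, so 58. Then 58 × 1.05 = 60.9, so 61 per arm and 122 in total, as stated. The t-based calculation gives 58.19 per arm, and 58.19 / 0.95 = 61.25. The sample size is not in dispute.

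**Assumptions.** The article gives neither the number of safety withdrawals nor their outcomes. Let k COMS participants be excluded with mean PWAR m, while the full-arm mean is μ. The excluded participants are taken to be people who would otherwise contribute an outcome. Then

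bias = (61μ − km)/(61 − k) − μ = k(μ − m)/(61 − k).

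**Exclusions in the COMS arm only, μ = 65 (bias in points, towards COMS):**

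| k of 61 | m = +45 | m = +20 | m = 0 | m = −50 |
|---|---|---|---|---|
| 1 (1.6%) | 0.33 | 0.75 | 1.08 | 1.92 |
| 3 (4.9%) | 1.03 | 2.33 | 3.36 | 5.95 |
| 6 (9.8%) | 2.18 | 4.91 | 7.09 | 12.55 |

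For example, with k = 3 and m = 0, the COMS mean becomes 65 × 61 / 58 = 68.36, a shift of 3.36 points or 17% of the 20-point target. With m = −50 (ulcers half as large again as at baseline), it becomes (3965 + 150) / 58 = 70.95, a shift of 5.95 points or 30%.

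**Cases with little or no bias.**
- If those excluded resemble their arm (m = μ), the bias is 0.
- If k are excluded in each arm with the same mean m, the net bias is k(65 − m)/(61 − k) − k(45 − m)/(61 − k) = 20k/(61 − k). That is +0.3 for 1 per arm, +1.0 for 3 and +2.2 for 6.
- With no true effect and such balanced exclusions, the bias is 0.

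**Type I error, no true effect (both arms 45%), COMS-only exclusions.** Here b = k(45 − m)/(61 − k), SE = 33 × √(1/(61 − k) + 1/61), and the two-sided rejection rate is Φ(b/SE − 1.96) + Φ(−b/SE − 1.96).

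- k = 3, m = 0: b = 2.33, rejection 6.7%.
- k = 3, m = −50: b = 4.91, rejection 12.8%.
- k = 6, m = 0: b = 4.91, rejection 12.6%.

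Without exclusions it is 5.0%.

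**Power.** By the normal approximation it is 91.7% with 61 against 61, and 91.1% with 58 against 61. The issue is bias, not loss of precision.

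**The case against.** A reader might infer that the exclusions will fall mainly on the COMS arm and that the primary comparison is therefore biased. The article does not support that:

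- It gives no safety-withdrawal rate for either arm. *Interim analyses* and *Composition of data monitoring committee (DMC)* describe the device as low or minimal risk.
- The exception covers any safety withdrawal, not only device-related ones. Both arms receive compression and debridement, and serious events can lead to withdrawal in either.
- Bias towards COMS needs exclusions that differ between arms in number or in outcome, and excluded COMS participants who do worse than their arm. If those excluded were healing better than average, the bias would run against COMS.

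These points stand, and they limit the claim to what can happen.

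Two further objections narrow the point. First, the article does not say whether withdrawal here means stopping treatment or leaving the study. Under the as-observed rule, anyone without a week-12 value is already absent from the ANCOVA. In that analysis the exception does added harm only through people who have a usable week-12 value. Second, and for the same reason, deleting the exception would not by itself retain those who have no week-12 value.

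None of this rescues the sentence. It is a rule stated in the article, not a detail left to an analysis plan. An analysis plan that follows it repeats the fault, and one that does not follow it contradicts the protocol. A low expected number of withdrawals is no reason to keep an exception that brings no analytical benefit.

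**Conclusion.** The exception is wrong as written: it contradicts the principle stated at the start of the same paragraph and can discard outcomes that the trial intends to collect. In this open-label trial it can fall unequally, plausibly more on COMS because only that arm can have device-related withdrawals, and it could then favour COMS. A forecast that it will do so goes beyond the document.

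The size is conditional throughout. One COMS-only exclusion costs at most about 2 of the 20 target points over the range considered. Three cost about 1 to 6 points. The effect becomes material at roughly 5 to 10% one-sided exclusion with poor outcomes, and it is small or absent when exclusions are balanced or unselective.

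**What to change.** - Delete the last four words of the exception sentence. State that all randomised participants stay in the ITT set in their allocated arm, whatever the reason for stopping treatment.
- State that week-12 outcomes collected after discontinuation are used in the primary analysis.
- For safety withdrawals without a week-12 value, turn the multiple imputation that the article names as an option into a committed analysis. Add a sensitivity analysis that assumes poorer outcomes for them.
- Report the number of safety withdrawals by arm, with reasons.

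This concerns the analysis set only and leaves the decision to stop treatment as it is. The cost is a few sentences in the protocol and analysis plan, the notification that the article requires for substantial changes to statistical methods, and a little more analysis work. The sample size stays at 122, with power of about 90% after 5% loss. *Trial status* reports that recruitment began in October 2025, with completion anticipated in December 2027, so the change is best made early, before outcomes accumulate.

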### Interim analyses

No formal interim analysis or early stopping rules are planned due to the modest sample size and low-risk profile of the intervention. Descriptive safety summaries will be periodically reviewed by the sponsor.

## Plans to give access to full protocol, dataset, and statistical code

Upon study completion, anonymized participant-level data and statistical code will be shared in a public repository (Yareta) under FAIR principles, after publication of primary results. Access will require a data use agreement ensuring non-commercial reuse and participant confidentiality.

### Composition of the coordinating center and trial steering committee

The coordinating center (HES-SO Geneva) oversees day-to-day operations, data management, and site communication. The trial steering committee includes the sponsor (SP) and co-investigators (CS, AS, AF). They meet quarterly to review progress, protocol adherence, and safety. No separate endpoint adjudication committee is appointed; blinded outcome assessment substitutes for this function.

### Composition of data monitoring committee (DMC)

Given the minimal risk of COMS and its CE-marked status, a formal independent DMC is not required. Safety monitoring will be conducted by the sponsor and coordinating center according to ISO 14155 standards. Any unexpected device-related serious adverse events will trigger immediate review and reporting.

### Adverse event reporting and harms

All serious adverse events (SAEs) will be recorded and reported. Only adverse events (AEs) deemed device-related will be reported to authorities. Severity and causality will be graded per ISO 14155 definitions. Annual safety summaries will be submitted to ethics committees. Investigators will assess and document each (S)AE from onset until resolution.

### Frequency and plans for auditing trial conduct

Independent monitoring will be conducted after the enrolment of every 25 participants, reviewing consent forms, CRFs, and adverse event documentation. The audit will be independent of investigators and sponsor staff, and reports will be archived electronically.

### Plans for communicating important protocol amendments

Any substantial amendments (e.g., changes in eligibility criteria, outcomes, or statistical methods) will be communicated promptly to ethics committees, trial registries (ClinicalTrials.gov), and all investigators. Updated versions will include version number and date. Summary of modifications and ethics committees’ decision will be sent to all investigators for filing in the Investigator Site File (ISF) binder.

